#### Data analysis

2.2.9.

The data will be analysed using Statistical Package for Social Sciences software (SPSS®) version 24.0 for Windows. Descriptive analysis will be used to characterize the sample. Within-group differences (t0 to t1 and t0 to t2) will be examined using paired sample *t*-tests. To evaluate change in primary and secondary outcomes between the two groups, we will perform ANCOVAs with treatment as the between-subject factor (MCT-Silver + TAU vs. TAU), the difference score of the outcomes (t1 – t0 and t2 – t0, respectively) as the dependent variable, and the baseline score of the respective outcome as the covariate. We chose ANCOVAs with difference scores instead of a repeated measures ANOVA to avoid regression to the mean and to control for potential baseline differences.

Intention-to-treat (ITT) analyses (including all participants who provided baseline data) using multiple imputation (MI) will be conducted. Analyses utilizing a complete cases sample (CC; including only complete data—i.e., baseline, post, and follow-up) will also be conducted. We will use analogous models to assess changes (t0-t1; t0-t2) for the secondary outcomes (WHOQOL-BREF item 1, DAS-18B, ERR-10-A, AAQ12, MCQ-30, MADRS, PHQ-9, RSE). We will also conduct planned moderation analyses for the primary outcome at post-assessment (BDI-II). Demographic characteristics (age, sex, education) and clinical characteristics (previous or current treatment, comorbid anxiety disorder, number of sessions attended) as well as baseline scores on secondary outcomes (WHOQOL-BREF item 1, DAS-18B, ERR-10-A, AAQ12, MCQ-30, MADRS, BDI, RSE) will be examined separately using moderation models as defined as defined by the PROCESS SPSS macro (model 1) [59]. Self-rated depression difference scores (t0–t1 and t0–t2) will be entered as the dependent variable (Y) and depression severity at t0 as the covariate.

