#### Randomization and blinding

2.2.3.

Eligible participants will be recruited at each institution (the mental health service of each hospital that agreed to take part in the study in Portugal) through telephone contact by the researchers in collaboration with the multidisciplinary team. The study will also be publicized in the media so that older adults can contact the researchers if they are interested in participating. A baseline assessment will be carried out and all instruments will be applied after informed consent from participants. All participants who agree to participate in the study will be assigned a code and will be randomly assigned to either MCT-Silver (experimental group where the intervention will be applied) or the control group (no stratification factors). This randomization will be performed using a computer program. The control group will not be administered the intervention (MCT-Silver). In both groups, treatment will be maintained as usual (Treatment As Usual – TAU) and participation in other interventions as well as use of medications will be carefully monitored. Study participants will be informed that they should not reveal which group they are in and will be reminded of this at each testing session. All participants will be re-assessed at the end of the intervention and 3 months after completion, with the application of all planned instruments. Assessments will be performed by the same rater before and after the intervention and at follow-up. Assessors will be trained in the administration of all instruments prior to the start of the study. A third researcher will inform patients of group assignment so that raters will remain blinded throughout the study. The Side Effects of Intervention questionnaire and patient satisfaction with MCT-Silver will be applied to the experimental group post-intervention (Table 1; Figure 1).

**Table 1 tab1:** Study schedule.

	Study period				
	Enrolment	Randomization	Intervention (8 weekly sessions)	Post (8 weeks)	Follow-up (3 months)
TIMEPOINT	T-1	T0		T1	T2
Enrolment:					
*Eligibility screen*	X				
*Informed consent*		X			
*Randomization*		X			
Interventions:					
*Treatment As Usual (TAU)*	X	X	X	X	X
*MCT-Silver*			X		
Assessments: *Baseline*		X			
*Post-intevention*				X	
*Follow up*					X

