##### Treatment as usual

2.2.5.1.

All participants (experimental and control group) will continue to receive treatment as usual (TAU) at their institution. TAU may consist of psychiatric and psychosocial treatment by a multidisciplinary team, which includes mental health psychiatric nurses, psychiatrists, psychologists, social workers, occupational therapists and other mental health professionals. TAU may also include treatment in community settings, day hospital and inpatient settings, as well as antidepressant medication, psychosocial rehabilitation, socialisation groups and psychoeducational and therapeutic groups. The care of participants in TAU will not be limited or influenced in any way. To control for TAU, we will carefully record participation in concurrent treatment. The control group will not participate in the MCT-Silver programme.

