##### Metacognitive training for depression (MCT-Silver)

2.2.5.2.

Metacognitive training (MCT) has its origins in 2003 with the development of “metacognitive training for psychosis” (Moritz et al., 2013, 2017). MCT has since been developed for other psychiatric disorders, e.g., depression (D-MCT; Moritz et al., 2013; Jelinek et al., 2015), and an adaptation of the D-MCT, called MCT-Silver (pilot study), has been developed for older adults with depression (Schneider et al., 2018). Although certain terms have been adapted for the Portuguese translation, case examples, exercises and general content were maintained to ensure consistency across countries. However, the intervention and examples can be tailored by the trainers to meet specific group needs of the group concerned (e.g., to reduce the length of sessions or tailor content to specific issues of group members). All information about this programme is available^2^ in English, German and Portuguese.

MCT-Silver is a manualized treatment program comprised of eight modules addressing common cognitive distortions and biases in information processing in depression as well as depression-related behaviors and metacognitive beliefs. Differing from D-MCT, MCT-Silver also includes components drawn from acceptance and commitment therapy as well as imagery rescripting. All content is supported by significant empirical work linking these processes to depression. The topics of MCT-Silver include the following: Modul 1: Mental filter; Module 2: Mood-congruent memory / false memories (Mathews and Macleod, 2005; Moritz et al., 2008); Module 3: “Should” statements (Egan et al., 2011; Mcgrath et al., 2012) and disqualifying the positive (Cane and Gotlib, 1985; Elliott et al., 1997) as well as acceptance of negative feelings (Hayes et al., 1996; Butler and Ciarrochi, 2007); Module 4: Values (Isaacowitz and Seligman, 2002; Hayes et al., 2006; Wrosch et al., 2013); Module 5: Exaggeration/Minimization (Garber and Hollon, 1980; Hoehn-Hyde et al., 1982; Cane and Gotlib, 1985; Wenzlaffand and Grozier, 1988) as well as Attribution Style (Carver and Ganellen, 1983; Wenzlaffand and Grozier, 1988); Module 6: Rumination and Withdrawal (Rood et al., 2009; Seidel et al., 2010; Wells, 2011); Module 7: Jumping to Conclusions (Strunk et al., 2006; Miranda et al., 2008), and Module 8: Self-Worth in Later Life (Davey et al., 2004; Orth et al., 2009; Holmes et al., 2016; Table 2).

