**Figure 2 fig2:**
[figure not shown]
Example of Module 7: Jumping to Conclusions.

Through interactive exercises and a structured multimedia presentation, MCT-Silver aims to convey knowledge about cognitive distortions, helps participants to reflect critically about and change the content of their thoughts, and acquire new strategies to solve problems. Each session lasts 45–60 min (Jelinek et al., 2022).

In the current study, MCT-Silver will be applied to the experimental group by mental health and psychiatry professionals with experience in the care of individuals with depression. A training course on the application of the MCT-Silver programme will be completed by these professionals prior to the start of the study. Administration of the training will also be monitored and supervised by the study PI ([name]). For adherence monitoring of the MCT-Silver application the sessions will be recorded, and no images of the participants will be taken to safeguard ethical issues.

MCT-Silver sessions will be applied once a week for a total of eight sessions. The intervention will be applied face-to-face in groups in a quiet room of the institution to which the group belongs.

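### MCT-Silver is delivered in groups, but the ANCOVA treats participants as independent; if outcomes correlate within groups, the standard error is understated and type I error exceeds nominal

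*Protocol article*

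**What the plan says.** All references are to the protocol article.

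- **Unit of randomisation (2.2.3).** Individual participants "will be randomly assigned to either MCT-Silver (experimental group where the intervention will be applied) or the control group (no stratification factors"). Section 2.4 describes stratification by sex and age instead. On either account the participant is the unit allocated, and neither account stratifies by institution.
- **Delivery (2.2.5.2).** "The intervention will be applied face-to-face in groups in a quiet room of the institution to which the group belongs". The exposure is repeated: "MCT-Silver sessions will be applied once a week for a total of eight sessions".
- **Tailoring (2.2.5.2).** The programme is manualised, but "the intervention and examples can be tailored by the trainers to meet specific group needs of the group concerned".
- **Control arm (2.2.5.1).** "The control group will not participate in the MCT-Silver programme". Treatment as usual, which both arms receive, may itself include "socialisation groups and psychoeducational and therapeutic groups".
- **Analysis (2.2.9).** For change to each follow-up time, "we will perform ANCOVAs with treatment as the between-subject factor (MCT-Silver + TAU vs. TAU"), with "the baseline score of the respective outcome as the covariate". Analogous models serve all secondary outcomes.

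No random effect, cluster-robust variance, or therapy-group or therapist term appears in 2.2.9 or elsewhere in the article.

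**The concern.** People who spend eight weekly sessions in the same room share a trainer, a group dynamic and possibly adapted content. Their outcomes may end up more alike than those of two people drawn from different groups. The trial creates this grouping in one arm only, so the design is partially nested: clustered in MCT-Silver, unclustered by design in the control arm.

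An ANCOVA with only treatment and baseline score takes the residuals as independent. If they are positively correlated within MCT-Silver groups, the mean of that arm is less precise than the model believes. The reported standard error is then too small, the confidence interval too narrow and the p-value too low. This would affect the primary BDI-II comparison at both follow-up times and every secondary comparison that uses the same model.

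**Working it through.** **Inputs.** From the article: individual randomisation, group delivery in one arm, and a model with treatment and baseline score. Not in the article, so assumed:

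- two-sided 5% significance level;
- 1:1 allocation;
- group size m from 4 to 10;
- ICC ρ (within therapy group, after adjustment for baseline) from 0 to 0.10;
- equal total variance in both arms.

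The article states no RCT sample size, power or error rate, so there is no figure of its own to reproduce.

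**Step 1. Variance ratio.** The design effect in the MCT-Silver arm is 1 + (m − 1)ρ; in the control arm it is 1. With equal arms, the true variance of the difference divided by the variance the ANCOVA assumes is

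R = {[1 + (m − 1)ρ] + 1} / 2 = 1 + (m − 1)ρ/2.

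For m = 8:

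- ρ = 0.01: R = 1 + 7 × 0.01/2 = 1.035; true SE is 1.017 times the reported SE
- ρ = 0.05: R = 1 + 7 × 0.05/2 = 1.175; 1.084 times
- ρ = 0.10: R = 1 + 7 × 0.10/2 = 1.350; 1.162 times

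**Step 2. Actual type I error.** In large samples, α = 2[1 − Φ(1.96/√R)].

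| Group size | ρ = 0 | ρ = 0.01 | ρ = 0.05 | ρ = 0.10 |
|---|---|---|---|---|
| 4 | 5.0% | 5.2% | 5.9% | 6.8% |
| 6 | 5.0% | 5.3% | 6.5% | 8.0% |
| 8 | 5.0% | 5.4% | 7.1% | 9.2% |
| 10 | 5.0% | 5.5% | 7.7% | 10.4% |

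**Step 3. Check by simulation.** The stated ANCOVA (change score on treatment and baseline) was simulated under the null with 20,000 runs per setting and an assumed baseline–outcome correlation of 0.5. The Monte Carlo standard error near 5% is √(0.05 × 0.95/20,000), about 0.15 percentage points. With groups of 8 and 16, 32 or 64 per arm, the rejection rates were:

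- 4.9–5.2% at ρ = 0
- 5.3–5.5% at ρ = 0.01
- 6.8–7.2% at ρ = 0.05
- 8.9–9.4% at ρ = 0.10

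These agree with the formula and barely change with sample size. Recruiting more groups of the same size does not remove the inflation.

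**Step 4. Does institution matter?** Institution effects are shared by both arms, so ignoring them works in the other direction. With one group per site and arms balanced within site, R = (1 − ρ_site) + (m − 1)ρ_group/2. For m = 8 and ρ_site = 0.05:

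- ρ_group = 0.05: R = 0.95 + 0.175 = 1.125, α about 6.5%
- ρ_group = 0.01: R = 0.95 + 0.035 = 0.985, α about 4.8%

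The offset depends on balance within site, which section 2.2.3 does not guarantee. A simulation with six sites, no group effect and ρ_site = 0.05 gave 4.4% with balance and 5.1% under simple randomisation. Neither shows material inflation from omitting institution.

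**The case against.** The strongest reply is that the inflation is conditional. It needs a positive within-group ICC, and the article supplies no ICC, group size, number of groups or significance level. Several features may keep between-group variation small: a manual, trainer training, supervision and recorded sessions. At ρ of 0.01 the excess is at most half a percentage point over the group sizes tried. This stands, and it is why the point is put as a conditional one.

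A reader might go further in five ways that the article does not support.

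- **Type I error certainly exceeds 5%.** At ICC 0 it does not.
- **Each group has its own trainers and its own content.** The article says only that trained professionals deliver the sessions, so one could lead several groups. Tailoring is permitted, not prescribed.
- **The missing institution term is part of the fault.** Under individual randomisation it does not cause the inflation (step 4).
- **The treatment effect is biased.** Ignoring the grouping affects the stated precision, not the estimate.
- **The RCT will be too small.** Section 2.2.4 leaves that calculation until after the pilot and gives no formula, so no shortfall can be charged to it.

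It is also fair to say that treatment as usual may include group activities. These are open to both arms and do not remove the clustering that MCT-Silver adds, but they make the treatment of every control as independent an assumption rather than a fact.

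Finally, an article condenses a fuller document. Here, however, it names the factor, the dependent variable and the covariate, and defends its model against repeated-measures ANOVA. That is a stated model, not a detail left open.

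**Conclusion.** The point holds in conditional form. The design groups participants in one arm and the stated ANCOVA takes no account of it. If outcomes correlate positively within MCT-Silver groups, the standard error is understated and type I error exceeds nominal. With two-sided 5%, 1:1 allocation, 8 per group and clustering in the MCT-Silver arm only, the actual error is about 5.4%, 7.1% and 9.2% at ICC 0.01, 0.05 and 0.10, and 5.0% at ICC 0.

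The omission is certain; its size cannot be fixed from the article. Balanced institution effects could offset part or, at a small group ICC, all of the inflation, but independence is not something the design secures.

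**What to change.** 1. Record a therapy-group identifier for every MCT-Silver participant.
2. In section 2.2.9, replace the ANCOVA at each time point with a partially nested mixed model. Treatment and baseline score are fixed effects, with a random intercept for therapy group in the MCT-Silver arm only. Each control stands alone. Use small-sample degrees of freedom such as Satterthwaite.
3. Keep the plain ANCOVA as a sensitivity analysis.
4. Carry the group identifier into the multiple imputation where feasible.
5. In the sample-size calculation due after the pilot, state the assumed group size and ICC. The pilot of 32 would give about 16 in MCT-Silver if allocated 1:1, or two groups of eight. That is too few to estimate an ICC usefully, so a planning range is needed.

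**Cost.** One recorded variable and revised analysis wording. At 8 per group the large-sample confidence interval widens by about 8% at ICC 0.05 and 16% at ICC 0.10. With few groups the variance component is poorly estimated and the interval may widen further. Planning for clustering can also raise the sample size. As an illustration only, with an assumed standardised difference of 0.5 and 80% power, 63 per arm becomes 75 at ICC 0.05 (63 × 1.175 = 74.03, rounded up) or 86 at ICC 0.10 (63 × 1.35 = 85.05, rounded up).

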### Aim

2.1.

The aim of this study is to evaluate the efficacy of MCT-Silver and its effects on depressive symptoms, dysfunctional beliefs, metacognitive beliefs, quality of life, ruminative responses, self-esteem and attitudes towards aging. The hypotheses that we want toexamine in this trial are the following:

Primary outcome: There will be a greater reduction in self-reported depression (as measured by the Beck Depression Inventory-II) for MCT-Silver vs. TAU (pre-post; pre-follow-up).Secondary outcomes: There will be a greater reduction in clinician-rated depression (MADRS), metacognitive beliefs (Metacognitions Questionnaire-30), self-reported depression (PHQ-9), dysfunctional beliefs (DAS-18B), ruminative responses (RRS), self-esteem (Self-Esteem Questionnaire), quality of life (WHO QOL-Bref??), and attitudes to aging (Attitudes to Aging Questionnaire) for MCT-Silver vs. TAU (pre-post; pre-follow-up).Tertiary outcome: Participants will rate the intervention positively on a satisfaction questionnaire administered after the 8-week intervention period.

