#### Study design

2.2.1.

This study represents an observer-blind, parallel-groups randomized controlled trial.

All procedures follow CONSORT (Consolidated Standards of Reporting Trials) guidelines and follow four phases: enrollment, intervention allocation, follow-up, and data analysis. The follow-up will occur 3 months after completion of the intervention. The trial has been registered at ClinicalTrials.gov (NCT05640492).

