### Ethical considerations and dissemination

2.3.

Approval will be obtained from the ethics committees of all institutions where the study will be carried out. All participants will be informed of the study’s objectives, methodology, benefits, and possible risks. All participants will sign a written informed consent expressing their agreement to participate in this study. Participants’ confidentiality will be ensured during all study procedures. Participants will be informed that they may withdraw their participation at any time without penalty or other consequence. Only research team members and healthcare professionals who care for participants have access to participant data. This data will be destroyed 5 years at the end of the study. If there is a need to change planned procedures, and that may have an impact on the execution of the study (e.g., changes in the study design, in the study objectives and in the study procedures), they will be reviewed by independent investigators and communicated to the ethics committees of all institutions where the study was carried out. The results of the study will be disseminated through oral communications and posters at conferences, and publications in scientific journals.

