Minimal negative side effects of D-MCT have been previously reported (Dietrichkeit et al., 2021). We anticipate similar findings, such as disappointment that the training did not result in (greater) symptom improvement and being more burdened by symptoms because patients may think about them more during the training. Attendance (i.e., coming to appointments) may also be perceived as stressful. It is also possible that patients could experience a clinically significance worsening of symptoms. In this case, participation in the study would be discontinued and, if necessary, participants would be offered assistance in identifying needed treatment.

This study includes many measurement instruments and were chosen to improve comparability with previous trails on MCT-Silver and D-MCT (see Jelinek et al., 2015) (Schneider et al., under review, see footnote 3). Nonetheless, completion of study measures can be burdensome and time-intensive for participants. Given that this is the first MCT-Silver trial in Portugal and participants are receiving a psychological intervention, we believe that the potential knowledge to be obtained from the study justifies participants’ time and potential burden related to participation in the study. Additionally, participants are allowed to discontinue testing and will not be penalized for this. Use of self-report measures is common in RCTs of psychological interventions and provide indications regarding patients’ perceptions of symptoms and suffering from these symptoms. Nonetheless, responses are impacted by many factors, including social desirability and insight, as well as reading competence and motivation, which may limit the validity of our findings. For this reason, we have also included a clinician-rated measure of depression (MADRS). The results of the RCT will be implemented to improve the training, provide information regarding efficacy among Portuguese patients (vs. TAU) and, in the case of efficacy, to support dissemination and uptake in Portugal, which would lead to a reduced treatment gap among older adults with depression.

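### The complete-case set requires all three visits, so the supplementary complete-case analysis at each time point discards outcomes that its own model could use

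*Protocol article*

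**What the plan says.** The protocol article, section 2.2.9 (Data analysis), fits one ANCOVA per contrast, with "the difference score of the outcomes (t1 – t0 and t2 – t0, respectively) as the dependent variable" and the baseline score as covariate. Secondary outcomes get analogous models.

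Two analysis sets are named. The first is broad: "Intention-to-treat (ITT) analyses (including all participants who provided baseline data) using multiple imputation (MI) will be conducted". The second is a complete-case sample, to be analysed as well, described as "including only complete data—i.e., baseline, post, and follow-up". There is one such sample, with no separate version for the T1 contrast. The section gives no purpose for it, and does not say in so many words which of the two analyses is primary.

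Two other sections bear on whether people will be lost between T1 and T2. Section 2.2.1 says "The follow-up will occur 3 months after completion of the intervention". Section 2.3 tells participants that "they may withdraw their participation at any time without penalty or other consequence".

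**The concern.** The T1 model uses the baseline and T1 scores and never uses T2. Requiring a T2 score for entry removes usable data without giving the model anything in return. The same holds in mirror image at T2 for a participant who missed the post-treatment visit but came back at 3 months.

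Two things are at stake, both confined to the complete-case results. The first is precision: the T1 estimate rests on fewer people than were measured. The second is selection: the T1 comparison is restricted by something that happens after T1. If leaving between T1 and T2 depends on the T1 score, and does so differently in the two arms, the complete-case T1 effect can be displaced. T1 is one of the two time points in the primary BDI-II hypothesis (section 2.1), so the complete-case T1 result is likely to be reported and read.

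**Working it through.** The article states no RCT sample size, SD or attrition rate; section 2.2.4 defers the sample size to the pilot. There is no planned figure to reproduce, and every numerical input below is an assumption.

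**1. Who is left out, by visit pattern (baseline present)**

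| T1 | T2 | t1–t0 model can use? | t2–t0 model can use? | In the stated complete-case set? |
|---|---|---|---|---|
| yes | yes | yes | yes | yes |
| yes | no | yes | no | no |
| no | yes | no | yes | no |
| no | no | no | no | no |

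Rows two and three are the needless losses. They follow from the definition alone.

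**2. Precision at T1**

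Let *a* be the share with T1 data and *c* the share with all visits. The share of T1 completers dropped is 1 − *c*/*a*. With unchanged residual SD and similar proportional loss in both arms, the standard error is multiplied by √(*a*/*c*).

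| *a* | *c* | Dropped | SE factor |
|---|---|---|---|
| 0.90 | 0.80 | 1 − 0.80/0.90 = 11.1% | √(0.90/0.80) = 1.06 |
| 0.85 | 0.75 | 1 − 0.75/0.85 = 11.8% | √(0.85/0.75) = 1.06 |
| 0.80 | 0.65 | 1 − 0.65/0.80 = 18.8% | √(0.80/0.65) = 1.11 |

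Seen another way, a T1-to-T2 loss of 5%, 10% or 20% gives factors √(1/0.95) = 1.03, √(1/0.90) = 1.05 and √(1/0.80) = 1.12. For an illustrative trial of 100 with nobody lost before T1 and a standardised effect of 0.6, T1 power is 85.1% with all T1 data. Under the three-visit rule it is 83.2%, 81.2% and 76.5% respectively.

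**3. Bias at T1**

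The T1 change was simulated for 1,000,000 participants and analysed by ANCOVA on arm and baseline, first with all T1 scores and then with the three-visit set. Assumptions: baseline BDI-II mean 25 and SD 9; T1 = 25 + 0.5 × (baseline − 25) − 3 + effect + error of SD 8; nobody lost before T1. Where T2 dropout is selective, its log-odds change by 0.08 per T1 point. Negative values favour MCT-Silver; the true effect shown is zero.

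| T2 dropout | Three-visit estimate at 10% dropout | At 20% dropout |
|---|---|---|
| unrelated to T1 score | 0.0 | 0.0 |
| worse scorers leave, same in both arms | 0.0 | 0.0 |
| worse scorers leave, MCT-Silver only | −0.5 | −0.9 |
| MCT-Silver worse leave, TAU better leave | −1.0 | −1.9 |

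Using all T1 scores gave 0.0 throughout. With a true effect of −5 points the shifts were about the same size. Under the null, exchanging the arm labels reverses the sign, so selection in TAU only gives about +0.5 to +0.9.

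A second check (null effect, SD 9, baseline–T1 correlation 0.6, 10–20% dropout, moderate to strong selection) gave 0.0 for equal selection, −0.3 to −1.1 for MCT-Silver only, and +0.3 to +1.1 for TAU only.

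**The case against.** The strongest reply is that the complete-case analysis stands beside an intention-to-treat analysis with multiple imputation that keeps every observed T1 score. A reader might infer from the complete-case rule that the trial's main T1 effect is conditioned on later dropout. The article does not support that: the imputed analysis comes first, and the complete-case one is an addition to it. This stands and limits the point to the supplementary estimate.

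A reader might also take the Discussion's remark on clinically significant worsening, "In this case, participation in the study would be discontinued", as proof that missing T2 depends on the T1 result. The remark follows a list of possible side effects of the training. It gives no time and is not tied to the T1 assessment. Worsening before T1 may leave no T1 score at all, and then neither definition could use that participant. So the passage does not establish the mechanism.

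Nor does the article say that the complete-case analysis is meant to check the imputation; that purpose would have to be supplied by the reader.

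A common three-visit set has a legitimate use: it compares T1 and T2 effects in the same people. That is a fair reason to keep one, but the article does not offer it, and it does not require giving up the per-contrast sets.

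Finally, the remedy is partial. Outcome-related loss before T1 would bias a baseline-plus-T1 set too, and outcome-related loss at T2 remains in the T2 analysis. This is also right. The change removes an avoidable selection and leaves the unavoidable one.

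**Conclusion.** The point holds for the supplementary complete-case analysis only. The definition discards observed T1 outcomes whenever anyone leaves between T1 and T2, and observed T2 outcomes whenever anyone misses T1 and returns. With the assumed retention pairs this costs 11–19% of T1 completers and raises the T1 standard error by about 6–11%.

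Bias is possible but not established. It needs T2 dropout that depends on the T1 outcome differently by arm. With selection in one arm only it is roughly 0.3 to 1.1 BDI-II points, and the sign depends on which arm loses its worse scorers. The larger shifts in the working need opposite selection in the two arms, which nothing in the article suggests. Severity is low, and the change is a free improvement.

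**What to change.** In section 2.2.9, define the complete-case set per contrast: baseline and T1 for the t1–t0 ANCOVA, baseline and T2 for the t2–t0 ANCOVA. Apply the same rule to the secondary outcomes and report n by arm for each contrast. If a common three-visit set is wanted so that T1 and T2 can be compared in the same people, keep it as an additional sensitivity analysis and give that reason. It would help to state in the same place that the imputed intention-to-treat analysis is primary, if that is the intention.

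The cost is a sentence or two of text. No new data, visits or participants are needed. The only consequence is that the complete-case n may differ between T1 and T2.

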#### Sample size calculation

2.2.4.

In RCTs to calculate the sample size, four factors are required: significance level, power analysis, difference between groups, and standard deviation (SD; Charles et al., 2009). As there is only one RCT in Germany that applied the MCT-Silver, we chose to conduct a pilot study, and the sample size calculation for the RCT is calculated *a posteriori*. For the pilot study, we will include 32 participants, as 15–20 participants are needed to ensure the scientific validity of the results of a pilot study (Hertzog, 2008). The results of the pilot study will provide information on the above four factors as they are necessary for the calculation of the sample size.

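### Number of sessions attended cannot be tested as a moderator with PROCESS model 1, because it arises after randomisation and is zero for everyone in the TAU arm

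*Protocol article*

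**What the plan says.** Section 2.2.9 (Data analysis) announces planned moderation analyses for the BDI-II. The candidate moderators are three demographic variables (age, sex, education), three clinical ones, and baseline scores on eight scales. The clinical group reads "clinical characteristics (previous or current treatment, comorbid anxiety disorder, number of sessions attended". The variables "will be examined separately using moderation models as defined as defined by the PROCESS SPSS macro (model 1"). The outcome is the BDI-II difference score, and the differences "will be entered as the dependent variable (Y) and depression severity at t0 as the covariate".

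The moderation sentences do not name the focal predictor. The only between-subject factor in the section is that of the ANCOVA, "treatment as the between-subject factor (MCT-Silver + TAU vs. TAU").

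On who can attend sessions, section 2.2.3 (Randomization and blinding) says "The control group will not be administered the intervention (MCT-Silver"), and section 2.2.5.1 (Treatment as usual) says "The control group will not participate in the MCT-Silver programme". Section 2.2.5.2 describes the programme: "MCT-Silver sessions will be applied once a week for a total of eight sessions". Nothing in the article limits the attendance model to the MCT-Silver arm, defines a session count for TAU, or treats attendance differently from the baseline moderators.

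**The concern.** A moderator of a randomised effect has to be defined in both arms and should be fixed before treatment begins. Attendance is neither. It accrues over the eight weeks after allocation, and only in the experimental arm. The model has to separate how the treatment effect varies with attendance from how outcome varies with attendance, yet no TAU participant has a non-zero value.

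The practical risk lies in what gets reported. The analyst will meet a singular model, a term will be dropped, and the surviving attendance coefficient may be written up as moderation. Readers would take it as dose-response evidence. Motivation and early improvement can drive both attendance and BDI-II change, and randomisation does not protect a comparison made inside one arm.

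**Working it through.** The article gives no figure to reproduce here. The size of the RCT is deferred until after the pilot (section 2.2.4: "the sample size calculation for the RCT is calculated" afterwards), and no sample size is needed. The question is whether the model is identified.

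**Inputs**
- X: randomised arm (inferred from the ANCOVA in section 2.2.9).
- W: MCT-Silver sessions attended, 0 to 8 in MCT-Silver (section 2.2.5.2) and 0 for all TAU participants (sections 2.2.3 and 2.2.5.1).
- C: depression severity at t0, the stated covariate.
- Model 1: Y = b0 + b1·X + b2·W + b3·X·W + b4·C, giving five columns [1, X, W, XW, C].

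**Case 1: TAU attendance coded 0**
- Let X = a in TAU and X = b in MCT-Silver. In TAU, XW = a·0 = 0 = b·W. In MCT-Silver, XW = b·W. So XW = b·W in every row.
- With 0/1 coding b = 1 and XW is simply W. The data determine b2 + b3 but not b3.
- Mean-centring does not help. (X − mX)(W − mW) = XW − mW·X − mX·W + mX·mW. Putting XW = b·W gives (b − mX)·W − mW·X + mX·mW, which still lies in the span of 1, X and W.
- Numerical check: rank 4 of 5 in all 18 settings (16, 50 or 200 per arm; coding 0/1, −0.5/0.5 or 1/2; centred or not). The arm sizes and attendance values were assumed; the algebra does not depend on them.

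**Case 2: TAU attendance set to missing and dropped listwise**
- Only MCT-Silver remains, X is constant and XW is proportional to W. The distinct columns are 1, W and C: rank 3 of 5.

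**Case 3: TAU attendance imputed**
- Section 2.2.9 plans multiple imputation for the ITT analyses. If it were applied here the model could run. The imputed values would describe attendance at a programme that TAU participants were never offered, and no observed TAU value could inform them.

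**Comparison models**
- A baseline moderator that varies in both arms: rank 5 of 5, so the interaction is estimable.
- Attendance without the product term, [1, X, W, C]: rank 4 of 4. The model runs, but since W varies only in MCT-Silver its coefficient is the within-arm attendance slope.
- Baseline BDI-II as moderator, with baseline BDI-II also as covariate: columns [1, X, B, XB, B], rank 4 of 5. The redundancy is B minus its duplicate and does not involve XB, so the interaction remains estimable.

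**Wording in the same section**
- The secondary-outcome list runs WHOQOL-BREF item 1, DAS-18B, ERR-10-A, AAQ12, MCQ-30, MADRS, PHQ-9, RSE. The moderator list, described as secondary outcomes, has the same order with BDI in the place of PHQ-9. BDI-II is the primary outcome (section 2.2.7).
- Moderation is introduced for post-assessment only, but the closing sentence enters both t0–t1 and t0–t2 differences.

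**The case against.** **X is not named, and sessions might include TAU groups.** Both points are fair. Treatment is the only between-subject factor the section offers, however, and the only sessions the article counts are the eight of MCT-Silver. If TAU group sessions were counted as well, the model could run, but the moderator would still be measured after randomisation and would mean something different in each arm.

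**This belongs in the analysis plan or full protocol.** That would answer a missing detail. Here the article itself fixes the variable, the macro and the model number, and a later document would have to contradict it.

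**It is one item in a secondary analysis.** This stands. The hypotheses in section 2.1 include no moderation hypothesis, and removing a few words cures the defect.

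Two stronger readings are tempting and are not supported:
- A reader might infer that the baseline-BDI model fails too, since it also shows rank 4 of 5. It does not fail: only a duplicated main effect is redundant. Even that depends on the t0 severity covariate being the BDI-II, which the text does not say, and the BDI entry looks like a slip for PHQ-9.
- A reader might count 14 moderators at two time points, 28 tests, and quote the chance of at least one false positive as 1 − 0.95^14 = 51% or 1 − 0.95^28 = 76%. Those figures assume independent tests, although the scales are correlated and the two differences share a baseline. They count a model that yields no interaction test (without it, 13 or 26 tests give 49% or 74%). Handling of multiplicity may also sit in a document not shown. They do not measure this defect.

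**Conclusion.** The point holds for one moderator. Taking X as randomised arm and sessions as MCT-Silver sessions, the arm-by-attendance interaction is not identified when TAU is coded zero (rank 4 of 5) or dropped (rank 3 of 5), and is not interpretable when TAU values are imputed. More participants, recoding or centring cannot change this. Any attendance coefficient left after a term is dropped is an observational slope within MCT-Silver.

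The reach is limited to 1 of 14 listed moderators (3 demographic + 3 clinical + 8 baseline scores), in a secondary analysis. The primary ANCOVA, the secondary ANCOVAs and the true baseline moderators stand as planned. It should be corrected because the model cannot be carried out as written; it does not threaten the trial's main conclusion. The BDI/PHQ-9 substitution and the disagreement over time points are minor drafting corrections.

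**What to change.** Delete number of sessions attended from the moderator list in section 2.2.9. If attendance is of interest, choose one of the following:
- Report its association with BDI-II change within MCT-Silver, labelled descriptive and non-causal.
- Optionally, estimate a complier-average effect at a prespecified attendance threshold with randomised arm as instrument, and state the assumption that attendance below the threshold has no effect on outcome.

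In the same edit:
- Correct BDI to PHQ-9 in the moderator list. If baseline BDI-II is wanted as a moderator, enter it once, together with its product with arm.
- State which scale the t0 severity covariate is.
- Reconcile the post-assessment restriction with the use of both difference scores.

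The cost is wording only, with no new data. A complier-average analysis would add a little work, using attendance counts that the present plan already requires.
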